Those with subclinical CAD (CAC score between 0 and 400) will then undergo same-day CTCA to identify plaque phenotypes and quantify plaque volume. Excellent image quality is essential for plaque volume measurement. Acquisitions are not performed at heart rates > 60 beats per minute. Participants are prepared with oral metoprolol premedication (50 mg in divided doses), and heart rate will be measured on arrival. Additional oral metoprolol or ivabradine may be used to aim for acquisition heart rate of < 60 bpm. Nitroglycerin will be administered ~ 1 min prior to contrast injection. A bolus of 100% lohexal was administered at 6mL/second followed by a 50mL normal saline chaser. Scanning is manually triggered when peak contrast enhancement is observed in the left ventricle, with no enhancement observed in the right ventricle. Tube current will be determined by automatic exposure control on the basis of X-ray attenuation in the initial scout images and the reconstruction kernel. Tube potential will be manually altered by the radiographer, with a default of 100kVp (range 80-120kVp) based on body habitus to minimize radiation dose. Scans will be prospective electrographic triggering, using 70–85% of the phase window with necessary widening on an individualized basis. The estimated radiation dose for full CTCA varies according to participants’ size and heart rate, but is routinely ~ 2 mSv [24]. 

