### Follow-up

Participants identified as low or high CAD risk based on the PCE risk score, as well as those in intermediate risk with a CAC of 0, will not be followed up. Participants with CAC > 0 and completed CTCA will be followed-up at 12-month post coronary CT appointment. Participants’ intervention plan, determined by participants and their GPs, will be obtained via telehealth.

At 24-month post coronary CT appointment, participants will be referred for a follow-up CT coronary angiography scan. Data including participants’ new disease diagnoses and intervention plans will be evaluated again via in-person clinic appointment. Participants will also be referred for fasting biochemistry tests as per baseline visit.

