### Endpoints

The primary endpoint of this study is to determine the prevalence of CAD (evidenced by CAC > 0) among cancer survivors who are classified as intermediate risk based on conventional risk assessment tool (PCE risk score).

Secondary endpoints include the absolute change in total coronary plaque volume over 24 months post CAC, assessed by an independent core laboratory. Additionally, different phenotypes of plaque, including high-risk plaque, non-calcified plaque and calcified plaque, will also be evaluated.

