### Statistical analyses

All data will be pooled and summarised with respect to demographic and baseline characteristics. Participants are then stratified based on their CAD risk (determined according to the PCE risk score). Exploratory data analyses will be performed using descriptive statistics, with categorical data being reported as number (percentage) whereas continuous variables as mean ± standard deviation (if parametric) or median [interquartile range] (if non-parametric).

Within the participants identified as intermediate risk by PCE, the proportion of participants with CAC > 0 will be determined, and the distribution of CAC score will be reported. Those who completed CTCA will then be included in the subsequent analysis identifying the absolute change in total coronary plaque volume, as well as the phenotypes of high-risk plaque, non-calcified plaque and calcified plaque, over 24-month post CAC. Participants will then be stratified based on statin use at 24-month post CAC and the differences in the absolute change in total plaque volume will be identified via t-test. The prevalence of critical CAD, defined as coronary stenosis > 70% identified via CTCA, will also be evaluated. The efficacy of this CAD risk evaluation will be compared with the broad community in two existing studies – (i) the CAUGHT-CAD trial [28] and (ii) the EDCAD-PMS trial (NCT04604353, ongoing).

Missing data will be explored and the nature of missing data will be identified. Multiple imputation by chain equation (MICE) will be applied to deal with data missing at random (MAR). Sensitivity analyses will be explored if missing data were identified as missing not at random (MNAR). These analyses will be on grounds of intention-to-treat.

Subgroup analyses, stratified based on age range, sex and cancer types, will also be conducted. A *p*-value of < 0.05 will be considered as statistically significance. All statistical analyses will be conducted using R (R Foundation for statistical computing).

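### The missing-data sensitivity analysis depends on first identifying data as missing not at random, which observed data cannot show, so 24-month plaque change may go unchecked

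*Protocol article*

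**What the plan says.** The Statistical analyses section handles missing data in three steps and then names the analysis basis:

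- First a diagnosis: "Missing data will be explored and the nature of missing data will be identified".
- Multiple imputation by chained equations (MICE) is used for data judged MAR.
- Then the conditional step: "Sensitivity analyses will be explored if missing data were identified as missing not at random".
- Finally: "These analyses will be on grounds of intention-to-treat".

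The section names no criterion, test or outside information for the diagnosis, and no endpoint.

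The endpoint that depends most on follow-up is in the Endpoints section: "Secondary endpoints include the absolute change in total coronary plaque volume over 24 months post CAC, assessed by an independent core laboratory". The scan it needs is in the Follow-up section: "At 24-month post coronary CT appointment, participants will be referred for a follow-up CT coronary angiography scan". The Methods part of the abstract restricts this endpoint to participants scanned on both occasions. Power calculations mentions attrition without a rate. The only other sensitivity analysis, in Limitations, adjusts for the treatment plan at follow-up and does not deal with missing scans.

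**The concern.** MAR and MNAR differ only in whether, given what was recorded, missingness still depends on the values nobody saw. Exploring the recorded values can count against data being missing completely at random, but it cannot tell MAR from MNAR. A sensitivity analysis exists to test an assumption that cannot be verified. If it waits until that assumption has been shown false, it may not be run, or it may be run at the analyst's discretion once results are visible. Even when triggered, the text promises only that such analyses will be explored.

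At stake is the 24-month plaque change, together with the comparison of that change by statin use. The article's Summary presents these as evidence on how treatment affects plaque progression.

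**Working it through.** The plan gives no figure to reproduce: no missing rate, no SD for plaque change and no expected number of paired scans. The check is therefore one of logic, plus an illustration whose inputs are all assumed.

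**1. Can the data trigger the rule?** A simulation of 200,000 participants had a standardised baseline value, about 20.3% of 24-month values missing with a probability that depends on baseline, and unseen values shifted by δ. With δ = 0 the data are MAR; with δ > 0 they are MNAR.

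| δ (SD) | Observed mean | Mean imputed under MAR | True mean |
|---|---|---|---|
| 0 | −0.010 | 0.001 | 0.000 |
| 0.25 | −0.010 | 0.001 | 0.051 |
| 0.5 | −0.010 | 0.001 | 0.102 |

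The observed data and the MAR result are the same in all three cases. Only the truth moves, so no exploration of those data could pick out the second and third rows.

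**2. Size of the bias in mean change.** Bias ≈ f × δ, where f is the missing share. The table above agrees: 0.203 × 0.25 = 0.051 and 0.203 × 0.5 = 0.102 after rounding. Over a range of assumed values:

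| f | δ = 0.25 SD | δ = 0.5 SD |
|---|---|---|
| 10% | 0.025 SD | 0.050 SD |
| 15% | 0.0375 SD | 0.075 SD |
| 25% | 0.0625 SD | 0.125 SD |

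**3. Against the precision.** Assume 200 baseline angiograms and 15% without a second scan, leaving 170. The standard error is 1/√170 = 0.077 SD.

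- δ = 0.5: bias/SE = 0.075/0.0767 = 0.98; coverage of a nominal 95% interval = Φ(1.96 − 0.98) − Φ(−1.96 − 0.98) ≈ 0.84.
- δ = 0.25: bias/SE = 0.0375/0.0767 = 0.49; coverage = Φ(1.47) − Φ(−2.45) ≈ 0.92.

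**4. The statin comparison.** The bias in a difference between two groups is f₁δ₁ − f₀δ₀. It is zero when the missing share and the shift are equal in users and non-users. With a shift of 0.5 SD in both groups but 25% missing in one and 10% in the other, it is 0.125 − 0.050 = 0.075 SD.

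**5. Which analysis would be exposed?** The abstract's both-scans population and the intention-to-treat statement do not settle whether a missed second scan is imputed. If it is, the result assumes MAR. If it is not, using the both-scans mean for everyone who had a baseline angiogram assumes that those who returned changed by the same amount as those who did not. Neither assumption has a check that is certain to be run.

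**The case against.** Several points on the other side are sound.

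- **The trigger could be met.** To identify MNAR need not mean to test for it. Table 1 lists new diagnoses, medication, treatment plan, adverse events and clinical outcomes at 12 and 24 months. Recorded reasons for missed scans could make MNAR plausible, and the same data in the imputation model would make MAR more credible. A reader might infer that the sensitivity analysis can never be run; the text does not support that. What remains is that the judgement is made after the data are seen and has no stated criterion.
- **MICE may not apply to this endpoint.** A reader might infer that imputed plaque values would stand alone. The abstract's both-scans wording means they might not be imputed at all, and the missing-data paragraph never names plaque change. The link to this endpoint is an inference, though a fair one.
- **The heart-rate limit for scanning is not evidence of MNAR.** Heart rate is recorded, so a scan cancelled on that ground fits MAR if heart rate is in the model. Premedication is also planned, and everyone due a second scan has completed a first.
- **Death is not ordinary missingness.** Plaque volume at 24 months does not then exist, and shifting an imputed value does not answer the question. The argument rests on missed scans among survivors.
- **Detail belongs in the SAP.** The shift range and software settings do. The conditional rule, however, is stated in the article, and an SAP that follows it would inherit the fault.
- **The primary endpoint is little exposed.** CAC > 0 is measured at baseline and no defect is shown there, so bounds on it are not called for.

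**Conclusion.** The point holds as a fault in a stated rule, not as an omission. The check on the missing-data assumption is conditional on a finding that observed data cannot deliver, so for 24-month plaque change it may not be run. Under the assumed 10–25% missing and 0.25–0.5 SD shift, the bias in mean change is about 0.025–0.125 SD. With 200 baseline scans and 15% missing, interval coverage falls to about 92% or 84% for shifts of 0.25 or 0.5 SD. None of these inputs comes from the document, so the figures show what could go unnoticed and do not predict the trial's actual bias. For the statin comparison, the bias largely cancels if loss and shift are similar in the two groups. The consequence is confined to a secondary endpoint. The wording should be corrected, but the prevalence result is not in doubt on this account.

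**What to change.** In Statistical analyses, remove the condition and replace it with text to this effect:

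- The main analysis of 24-month plaque change uses MICE under MAR for participants with a baseline angiogram who are alive at 24 months, with the recorded 12- and 24-month clinical data in the imputation model. Deaths are reported separately.
- Whatever the exploration of missing data shows, a delta-adjusted (pattern-mixture) analysis is always reported for this endpoint. It covers a range of shifts fixed in advance, for example 0 to 0.5 SD more progression in those without a second scan, and gives the tipping point at which the conclusion changes.
- The abstract's both-scans wording is aligned with whichever population is chosen. If the both-scans analysis is kept, it is labelled as such and accompanied by the same delta-adjusted analysis.

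The cost is a few sentences and a small amount of extra analysis. No new data, visits or procedures are needed.

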### Power calculations

Sample size calculations were based on our previous study in a non-cancer cohort (CAUGHT-CAD trial), which demonstrated that 48% of participants classified as intermediate risk had CAC > 0 and warranting preventative therapy. Given the increased cardiovascular risk associated with cancer survivorship, we hypothesized a 10% higher prevalence of significant CAD in our study population compared to the general population. Using a two-sided alpha of 0.05 and power of 80%, we calculated that 839 participants would be required to detect this anticipated difference in CAD prevalence. This sample size accounts for potential attrition and provides sufficient statistical power to address our primary endpoint of CAD prevalence in intermediate-risk cancer survivors.

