### Limitations

The key limitation of this study is the challenges in risk stratification accuracy. The initial risk stratification is fully based on PCE, which may underestimate the proportion of cancer survivors who require further screening. While universal scanning would provide more complete data on PCE’s performance in this population, our study design deliberately mirrors real-world clinical practice constraints, where resource limitations necessitate selective screening approaches. This pragmatic approach, though potentially missing some at-risk individuals, aims to establish an implementable framework for cardiovascular risk assessment in cancer survivorship care. Similarly, CAC may not detect all forms for subclinical CAD, particularly in early stages or in cases where plaque is non-calcified. These could potentially limit the validity of the study outputs. No screening test is perfect, and it is possible for a patient to have asymptomatic, severe non-calcified atherosclerotic disease that would be missed on a CAC scoring test and lead to inappropriate delay of treatment. Current evidence suggests that this clinical scenario is very uncommon, with a meta-analysis indicating that prevalence of obstructive non-calcified plaque is 1.1% and we may therefore incorrectly designate approximately 9 patients as low risk in our target sample size [41]. This does not justify the cost and radiation exposure of this strategy. Our methodology in employing CAC as an additional screening tool aligns with current clinical practice guidelines and offers a balance between diagnostic yield and resource utilization in risk stratification. While we do provide a guideline and recommendation to participants and their GPs, the final intervention to manage CAD risk lies at the GPs’ discretion and their discussion with the participants. Thus, the differences in clinical care might result in disparity in the outcome of interest. We plan to address this by conducting sensitivity analyses to adjust for participants’ treatment plan at follow-up.

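### For a single cohort, the 10% effect, the sample size of 839 and the claim that it covers attrition cannot be reconciled as written

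*Protocol article*

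**What the plan says.** The Power calculations section of the protocol article takes its reference value from an earlier non-cancer trial in which "48% of participants classified as intermediate risk had CAC > 0 and warranting preventative therapy". It continues: "we hypothesized a 10% higher prevalence of significant CAD in our study population compared to the general population". With a two-sided alpha of 0.05 and 80% power, "we calculated that 839 participants would be required to detect this anticipated difference in CAD prevalence". It then adds: "This sample size accounts for potential attrition and provides sufficient statistical power to address our primary endpoint".

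The section does not state the scale of the 10%, the test, or a loss rate. Two other places bear on how to read 839:

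- Statistical analyses says that the results "will be compared with the broad community in two existing studies", so the comparators are external and no control group is recruited.
- Limitations applies a 1.1% prevalence of obstructive non-calcified plaque and concludes that "we may therefore incorrectly designate approximately 9 patients as low risk in our target sample size". Since 1.1% of 839 is 9.2, the authors treat 839 as the size of this cohort.

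**The concern.** A 10% higher prevalence than 48% can mean 58% (10 points) or 52.8% (4.8 points). The planned difference differs about two-fold between these readings, and the one-sample size more than four-fold. The article fixes three things at once: the effect, the number, and the assurance that the number already covers losses. If they cannot all hold for one cohort, then either the attrition assurance has no substance or 839 was computed for a design with two groups.

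This is the only justification given for the sample size of the primary endpoint. A reader cannot tell whether the study was planned around a 4.8-point or a 10-point difference, or what power remains once some scans are missing.

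**Working it through.** **Inputs.** From Power calculations: p0 = 0.48, two-sided alpha 0.05 (z = 1.960), power 80% (z = 0.842), stated n = 839. The alternative is p1 = 0.48 × 1.10 = 0.528 (relative) or p1 = 0.48 + 0.10 = 0.58 (absolute). All loss rates below are assumptions, because the article gives none. I take 839 to count intermediate-risk participants, the population of the primary endpoint.

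**Formulas.**
- One sample against a fixed p0: n = [(1.960·√(p0(1−p0)) + 0.842·√(p1(1−p1))) / (p1−p0)]²
- Two samples, pooled variance under the null, per group: n = [(1.960·√(2p̄(1−p̄)) + 0.842·√(p0(1−p0)+p1(1−p1))) / (p1−p0)]², where p̄ is the mean of p0 and p1
- Power, one sample: Φ[((p1−p0)√n − 1.960·√(p0(1−p0))) / √(p1(1−p1))]

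**Reproducing 839: relative reading, one sample.** √(0.48·0.52) = 0.4996 and √(0.528·0.472) = 0.4992, so n = [(1.960·0.4996 + 0.842·0.4992)/0.048]² = 849.9, that is 850. The stated 839 is 1.3% lower. The printed 48% may be rounded. With a further 10% relative increase, p0 = 0.475 gives about 868, p0 = 0.483 gives 839.4, and p0 = 0.485 gives about 832. The plan's figure is therefore reproduced, but as the number before attrition. Even at the most favourable end of the rounding, the slack is (839 − 832)/839 = 0.8%.

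**All readings.**

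| Reading | p1 | Test | Required before loss |
|---|---|---|---|
| Relative | 52.8% | one-sample v 48% | 850 |
| Relative | 52.8% | two-sample | about 1,702 per group |
| Absolute | 58% | one-sample v 48% | 195 |
| Absolute | 58% | two-sample | 390 per group, 780 in total |

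**The other route to 839.** 780/(1 − 0.07) = 838.7, that is 839. With a continuity correction the two-group total is 820, and an assumed 2% loss takes it to 837. Either way, the number is the total of two groups.

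**Power of the one-sample test with 839 recruited.**

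| Assumed loss | Evaluable | Power v 52.8% | Power v 58% |
|---|---|---|---|
| 0% | 839 | 79.5% | >99.9% |
| 5% | 797 | 77.4% | >99.9% |
| 10% | 755 | 75.2% | >99.9% |
| 20% | 671 | 70.2% | >99.9% |

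On the relative reading, a real allowance would take 850 to 850/0.95 = 895, 850/0.90 = 945 or 850/0.80 = 1,063.

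**The case against.** The strongest reply is that 839 is not an arithmetic error. It lies within 1.3% of 850, it is matched if the unrounded reference is 48.3%, and 79.5% power is 80% for practical purposes. This stands. A reader might infer that 839 does not follow from the stated inputs; the documents do not support that.

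A second reply is that the attrition sentence has not been shown to be false. The two-group route, with an absolute 10 points and about 7% loss, keeps both the effect size and the attrition claim. This also stands as far as it goes: the article does not name the test, and it does plan a comparison with other studies. So one may not conclude that the attrition claim must be untrue or the effect misdescribed. But this route moves the problem elsewhere. It makes 839 the total of two groups, whereas the study recruits one cohort and Limitations uses 839 as that cohort's own target.

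Third, the test, the comparator's size and the loss rate may be set out in a fuller document that is not shown. Their absence alone would be no finding. The point here is that the effect, the number and the assurance that the article does print do not fit one design.

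Fourth, the primary endpoint is a prevalence, and its confidence interval will show what the data exclude whatever effect was planned. That is correct and limits the consequence: the justification of the sample size is at fault, not the interpretability of the estimate.

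The phrase about significant CAD, where the endpoint is CAC > 0, is loose wording. The preceding sentence ties the 48% to CAC > 0, and no number changes.

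**Conclusion.** The point holds in a limited form. Two routes lead to 839, and each conflicts with something that the article says:

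- **Relative, one-sample:** it fits the single cohort, but 850 are needed before loss (about 832 to 868 across the rounding of 48%), so the stated attrition allowance is essentially nil. Power falls from 79.5% to between 77.4% and 70.2% at assumed losses of 5% to 20%.
- **Absolute, two-group:** it leaves room for about 7% loss, but it is not this design. A single cohort would need 195 before loss.

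A reader might infer that the study is underpowered. The documents do not establish this: the shortfall exists only on the relative reading and is modest at moderate losses, and on the absolute reading 839 is far more than needed.

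The figures assume normal approximations, a 48% reference treated as fixed in the one-sample case, and 839 counted in intermediate-risk participants. The loss rates are illustrative.

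**What to change.** In Power calculations:

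1. Give the alternative as a percentage (52.8% or 58%).
2. Name the test: one-sample against a fixed 48%, or two-sample with the comparator's number.
3. If the relative one-sample calculation was used, delete the statement that 839 accounts for attrition, and restate the power at the expected evaluable number of intermediate-risk participants.
4. If the two-group calculation was used, restate the number that this cohort itself needs, with the loss rate assumed.
5. As a minor tidy-up, refer to CAC > 0 instead of significant CAD.

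The cost is a few sentences and, on the relative reading, a slightly less favourable stated power. The correction itself changes no procedure or recruitment.

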**Methods:**

The REDEEM-CAD (Risk-guidEd DisEasE Management plan to prevent CAD in patients with previous cancer) study is a prospective cohort study conducted in Victoria and Tasmania, Australia aiming to evaluate the efficacy of a comprehensive CAD screening strategy. Cancer survivors aged *≥* 40 years with cancer treatment ≥ 5 years prior are eligible for the study. Consented participants will be stratified into low, intermediate or high risk of major atherosclerotic adverse events based on clinical assessment and biochemistry tests. Subsequently, those within the intermediate risk will be referred for coronary artery calcium (CAC) scoring, with computed tomography coronary angiography (CTCA) completed where CAC > 0 and < 400. Participants with high risk or CAC > 400 will be informed about strategies (including lipid-lowering therapy) to manage asymptomatic CAD. Those with low clinical risk or CAC = 0 will conclude their participation while those with CTCA imaged at baseline will be referred for a follow-up CTCA 2-year post-baseline. The primary endpoint is to identify the prevalence of CAD, identified via CAC scoring, among cancer survivors classified as intermediate risk. Secondary endpoint includes the absolute change in total coronary plaque volume over 24 months among those imaged at baseline and follow-up.

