## Preliminary data

The REDEEM-CAD study initiated on October 2023. Table 2 demonstrates participants’ sociodemographic and clinical characteristics at baseline. In summary, participants had a median age of 64 [54–70] years and the majority of them were survivors from breast cancer (*n* = 49). The proportion of survivors who went through chemotherapy and radiotherapy were 66% and 86%, respectively. The overall comorbidity burden was mild to moderate (median CCI: 2 [0–3]), with dyslipidaemia being the most prevalent comorbidity among the survivors (*n* = 21). The total cholesterol, high-density lipoprotein (HDL) and low-density lipoprotein (LDL) levels were 5.4 [4.6–5.9], 1.6 [1.4-2.0] and 3.1 [2.4–3.7], respectively. Based on the clinical assessment and pathology results, survivors showed median PCE risk score of 6.0% [2.1–11.8], with the distribution of low-, intermediate- and high-risk being *n* = 47, *n* = 41 and *n* = 12, respectively. The median CAC score for the survivors within intermediate risk were 14 [0–45].

**Table 2 Tab2:** Baseline characteristics of the consented participants

	Total (*n* = 100)	Low PCE risk (*n* = 47)	Intermediate PCE risk (*n* = 41)	High PCE risk (*n* = 12)
Age, years	64 [54–70]	55 [45–60]	66 [64–71]	74 [72–77]
Male, n	19	3 (6.4%)	9 (22.0%)	7 (58.3%)
Body mass index, kg/m^2^	26.3 [24.1–30.7]	25.6 [23.9–27.7]	26.7 [24.3–31.9]	27.9 [25.2–30.6]
Cancer type, n				
Breast cancer	49	23 (48.9%)	24 (58.5%)	2 (16.7%)
Lymphoma	39	19 (40.45%)	12 (29.3%)	8 (66.7%)
Leukaemia	2	1 (2.1%)	1 (2.4%)	0
Other cancer type	9	4 (8.5%)	4 (9.8%)	1 (8.3%)
Smoking status, n				
Current smoker	2	1 (2.1%)	1 (2.4%)	0
Former smoker	34	17 (36.2%)	13 (31.7%)	4 (33.3%)
Never smoke	64	29 (61.7%)	27 (65.9%)	8 (66.7%)
Blood pressure, mmHg				
Systolic blood pressure	130 [119–144]	121 [111–132]	135 [128–149]	141 [127–160]
Diastolic blood pressure	80 [72–89]	79 [71–86]	81 [72–90]	81 [71–88]
Heart rate, bpm	76 [69–81]	76 [70–80]	76 [69–81]	71 [64–88]
Cancer treatment, n				
Chemotherapy	66	35 (74.5%)	22 (53.7%)	9 (75%)
Radiotherapy	86	44 (93.6%)	34 (82.9%)	8 (66.7%)
Comorbidities, n (%)				
Atrial fibrillation	2	0	1 (2.4%)	1 (8.3%)
Arrhythmia	7	5 (10.6%)	1 (2.4%)	1 (8.3%)
Cerebrovascular disease	2	1 (2.1%)	1 (2.4%)	0
Chronic kidney disease	1	0	0	1 (8.3%)
Deep vein thrombosis	3	1 (2.1%)	0	2 (16.7%)
Diabetes	5	1 (2.1%)	1 (2.4%)	3 (25%)
Dyslipidaemia	21	9 (19.1%)	7 (17.1%)	5 (41.7%)
Psychiatric disorder	4	2 (4.3%)	2 (4.9%)	0

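### The 839 for the primary endpoint is not tied to a population: only 41 of 100 consented survivors were intermediate risk, and no allowance for that yield is shown

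*Protocol article*

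**What the plan says.** All of this is in the protocol article.

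- **Power calculations.** The reference figure is that "48% of participants classified as intermediate risk had CAC > 0 and warranting preventative therapy". The plan then says "we hypothesized a 10% higher prevalence of significant CAD in our study population compared to the general population". The test is set at a 5% two-sided significance level with 80% power, and on that basis "we calculated that 839 participants would be required to detect this anticipated difference in CAD prevalence". It adds: "This sample size accounts for potential attrition and provides sufficient statistical power to address our primary endpoint". No attrition rate and no intermediate-risk share are given.
- **Endpoints and Statistical analyses.** The primary endpoint is the proportion with CAC above 0 among those whose PCE score puts them at intermediate risk.
- **Abstract (Methods), Patient selection and Coronary risk assessment.** "Consented participants will be stratified into low, intermediate or high risk of major atherosclerotic adverse events". Eligibility has no PCE criterion. Low- and high-risk participants leave the study after classification, and only intermediate-risk participants go on to CAC scoring.
- **Preliminary data.** The 100 consented participants are reported "with the distribution of low-, intermediate- and high-risk being" 47, 41 and 12.
- **Limitations.** From a 1.1% prevalence of obstructive non-calcified plaque, the article concludes that "we may therefore incorrectly designate approximately 9 patients as low risk in our target sample size".

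**The concern.** The reference rate and the endpoint both belong to the intermediate-risk stratum, so a calculation built on them returns a number of intermediate-risk people with a CAC result. Recruitment counts something else: everyone who consents, of whom more than half have so far been low or high risk and so provide no primary-endpoint data. Their exit is part of the design. It is not attrition, so the remark about attrition does not cover it.

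If recruitment stops at 839 consents, the primary analysis would rest on well under half that number. The prevalence estimate would be less precise than the plan implies, and, depending on the effect size meant, a null comparison with 48% could be taken as adequately powered when it is not. If recruitment is meant to reach 839 scans, the enrolment that the study needs appears nowhere in the article.

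**Working it through.** **Inputs.** From Power calculations: reference p0 = 0.48, two-sided alpha 0.05 (z = 1.960), power 80% (z = 0.842), N = 839. The alternative p1 is 0.528 if the 10% is relative (0.48 × 1.10) and 0.58 if it is absolute (0.48 + 0.10). From Preliminary data: intermediate-risk share 41/100 = 0.41, Wilson 95% CI 0.319 to 0.508. I take 48% as a fixed comparator unless stated otherwise, and I assume that every intermediate-risk participant is scanned.

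**Step 1: reproduce 839.** One-sample test of a proportion:

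n = [1.960·√(p0(1−p0)) + 0.842·√(p1(1−p1))]² / (p1−p0)²

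| Reading | Computed n |
|---|---|
| One-sample, relative (48% vs 52.8%) | 850 |
| One-sample, absolute (48% vs 58%) | 195 |
| Two-sample, relative | 1,703 per group |
| Two-sample, absolute | 390 per group, 780 in total (820 with continuity correction) |

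Only the one-sample relative reading comes close to 839 from stated inputs alone (1.3% off; power at 839 is 79.5%). Because 850 already exceeds 839, that reading leaves no room for the attrition allowance that the text claims. The two-sample absolute total reaches 839 if attrition is taken as 7% (780/0.93 = 838.7). That rate is an assumption, and the total would then include a comparator group that this single-cohort study does not recruit.

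**Step 2: if 839 is the enrolled total.**

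- Analysable: 839 × 0.41 = 344. Over the CI of the share: 839 × 0.3187 = 267 to 839 × 0.508 = 426.
- Precision: 1.96·√(0.528 × 0.472/344) = 5.3 points, against 1.96·√(0.528 × 0.472/839) = 3.4 points. With 0.58 in place of 0.528 the first figure is 5.2, so the loss hardly depends on the effect size.
- Power, one-sample: Φ{[(p1−p0)√n − 1.960·√(p0(1−p0))] / √(p1(1−p1))}.
  - Relative, n = 344: Φ(−0.178) = 42.9% (exact binomial 42.0%). At n = 267 and 426 it is 35% and 51%.
  - Absolute, n = 344: Φ(1.774) = 96%.
- Power, two-sample absolute, 344 against an equal-sized comparator (assumed size): 75%.
- Difference from a fixed 48% detectable with 80% power at n = 344: solving the formula in Step 1 gives p1 − 0.48 = (1.960 × 0.4996 + 0.842 × 0.4969)/√344 = 7.5 points, against 4.8 points at n = 839.

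**Step 3: if 839 counts intermediate-risk scans.** Power is 79.5% on the relative reading. The consents needed are 839/0.41 = 2,047, or about 2,050.

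**Step 4: the Limitations figure.** 839 × 0.011 = 9.2, which treats all 839 as CAC-scanned. With 344 scanned, 344 × 0.011 = 3.8, or about 4.

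**The case against.** The strongest reply is that 839 may already mean intermediate-risk participants. The paragraph starts from a rate in intermediate-risk people and ends by naming the intermediate-risk endpoint, and the figure of about 9 in the Limitations fits 839 being the scanned number. On that reading the power claim is sound, and the Limitations figure needs no change. This cannot be excluded. Against it, the article elsewhere uses the word participants for everyone who consents, including those who turn out to be low or high risk. Even if the reply is right, the need for about 2,050 consents is not stated.

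A second reply is that the 10% may be absolute, in which case 344 scans would be ample against a fixed 48%. That also stands as a possibility, although a fixed-comparator calculation would then have asked for only 195. The two-group version reaches 839 only with an attrition rate that the article does not give.

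A third reply is that a recruitment multiplier and an attrition rate may sit in the full protocol. Their absence here is not the point. The article itself asserts that 839 gives sufficient power for this endpoint, and that assertion cannot be read without knowing whom 839 counts.

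A reader might infer that the trial's 80% power has been shown to fall to 43%. The documents do not support so firm a statement. It needs 839 to be the enrolled total and the 10% to be relative, neither of which is stated, and the 41% share comes from only 100 people.

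**Conclusion.** The concern holds in conditional form. What is certain from the article is that the endpoint is confined to one risk stratum, that consent precedes classification, that 41 of 100 consented participants fell in that stratum, and that the sample-size paragraph neither names the population counted nor allows for the yield.

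The consequence depends on the reading:

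| 839 counts | 10% is | Comparator | Consequence |
|---|---|---|---|
| Enrolled | relative | fixed 48% | power about 43% (35% to 51%) |
| Enrolled | absolute | fixed 48% | power about 96% |
| Enrolled | absolute | equal-sized group (assumed) | power about 75% |
| Intermediate-risk scans | relative | fixed 48% | power about 80%, about 2,050 consents |

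In every enrolled-total row the prevalence is estimated to within about 5.3 points instead of 3.4. This matters in its own right, because the primary endpoint is a prevalence. All rows assume that the 41% share persists and that every intermediate-risk participant is scanned.

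**What to change.** In Power calculations, state which population 839 counts, the assumed intermediate-risk share, and whether the 10% is relative or absolute. Give the attrition rate that the text says is included. Then restate the figures to match:

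- **If 839 is enrolment:** 839 enrolled is expected to give about 344 intermediate-risk participants (41% observed), a 95% CI half-width of about 5.3 points, and 80% power for a difference of about 7.5 points from a fixed 48%.
- **If 839 is intermediate-risk participants with a CAC result:** say so, and give the implied enrolment of about 2,050.

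In the Limitations, put the count of wrongly designated patients on the same denominator: about 9 if 839 are scanned, about 4 if 344 are.

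The cost is one rewritten paragraph and one figure. The stated power, precision or enrolment will look less favourable. No extra participants are needed if the figure is restated as enrolment; keeping 839 as the number of scans means committing to the larger enrolment.
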